**Methods/Design:**

We will conduct a three parallel arm, randomized trial. A convenience sample of adults aged 18 to 25 years attending three EDs in Pittsburgh, PA and willing to participate in the study will be screened for hazardous alcohol consumption. Participants identified as hazardous drinkers will then be allocated to either 12 weeks of weekly SMS drinking assessments with feedback (SA+F), SMS drinking assessments without feedback (SA), or a control group. Randomization will be via an independent and remote computerized randomization and will be stratified by study site. The SA+F group will be asked to provide pre-weekend drinking intention as well as post-weekend consumption via SMS and will receive feedback messages focused on health consequences of alcohol consumption, personalized normative feedback, protective drinking strategies and goal setting. Follow-up data on alcohol use and injury related to alcohol will be collected through a password-protected website three, six and nine months later. The primary outcome for the study is binge drinking days (≥4 drinks for women; ≥5 drinks for men) during the previous month, and the main secondary outcome is the proportion of participants who report any injury related to alcohol in the prior three months.

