### Setting

Recruitment is occurring within three EDs at the University of Pittsburgh Health Care System, including two Level I trauma centers and one Level II trauma center. Patient characteristics from the fiscal year 2011 include an average of 11,349 patients aged 18 to 25 years of age, among whom 64% were female, 72% Caucasian, and 24% African American. Hispanic ethnicity was estimated as 2%.

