### Participants

Inclusion criteria for participation in the TRAC trial comprise the following: age 18 to 25 years, English-speaking, hazardous drinking behavior (Alcohol Use Disorder Identification Test for Consumption: AUDIT-C scores of >3 for women or >4 for men) [32] and last month binge episode. Exclusion criteria include the following: past treatment for drug or alcohol disorder, current treatment for psychiatric disorder (including depression). Participants are also excluded if they do not own a cell phone with text messaging. Young adults with hazardous drinking who are not eligible or decline study participation are provided the same referral and educational materials as study participants, but they will not participate in any further assessments or monitoring. These young adults are directed to contact their primary care physician or a local community resource about reducing their alcohol consumption. Eligible and interested participants sign and date the Informed Consent Form prior to any further baseline clinical and demographic data, randomization and treatment allocation. We collect multiple points of contact from each participant, including at least one ‘locator’ if we cannot find the participant for follow-up.

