For those patients who are eligible and enroll in the TRAC trial, we will collect further demographics including co-habitation (‘Who do you live with?’), marital status, and current employment. Alcohol consumption will be measured using the Timeline Followback (TLFB) procedure [40]. Using a calendar, participants provide retrospective estimates of their daily drinking over the 30 days prior to the interview date. Memory aids will be used to enhance recall (for example, visual calendars with key dates and holidays serve as anchors for reporting drinking; a visual chart of standard drink sizes reduces variability in quantity). Alcohol-related injuries are measured using the Injury Behavior Checklist (IBC) [41]. The IBC asks participants about how often each of the 17 injuries had occurred in the past three months. If a participant affirms that an injury had happened, subsequent questions about the use of alcohol prior to injury occurrence and whether they were treated by a doctor are asked. Drug use in the past three months is measured using the National Institute on Drug Abuse (NIDA)-modified Alcohol, Smoking and Substance Involvement Screening Test (ASSIST). The ASSIST was developed by the World Health Organization and developed principally for use in primary health care settings [42]. Depression and anxiety are measured using a two-item depression scale and a two-item anxiety scale, that is, the Patient Health Questionnaire for Depression and Anxiety (PHQ-4) [43]. Drinking norms are measured through a single question: ‘How much do you drink compared to others your age?’ where responses can range from ‘much less’ to ‘much more’, anchored by option ‘the same’. Behavioral control is measured through the question: ‘How sure are you that you could resist “drinking to get drunk” when out with friends?’ where responses can range from ‘not sure at all’ to ‘completely sure’.

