### Follow-up measures

Follow-up data will be obtained through a password-protected website at three-, six- and nine-months after ED discharge. At each time point, alcohol consumption data in the last 30 days will be collected using the TLFB procedure. Alcohol-related injuries are measured using the IBC, drug use measured using the ASSIST, depression and anxiety using the PHQ-4, and drinking norms and behavioral control through identical questions to baseline. At nine-month follow-up, all participants will complete a structured diagnostic assessment for determining Diagnostic and Statistical Manual of Mental Disorders, 4th Edition (DSM-IV) diagnoses for alcohol abuse and dependence. Individuals who meet alcohol abuse or dependence criteria will also receive alcohol treatment referrals.

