### Outcomes

The primary outcome is the change in mean number of binge drinking days during the previous 30 days from baseline to follow-up using the TLFB. The main secondary outcome is the change in the proportion of participants with at least one alcohol-related injury (IBC) from baseline to follow-up. Other secondary outcomes include the mean number of drinks consumed per drinking day. We will examine the potential cognitive and motivational processes that mediate the influence of our intervention on alcohol consumption, specifically pre-weekend drinking intentions and goal-setting rates over the course of the 12-week SMS dialog. We will explore whether ED presentation related to alcohol and co-occurring drug use at baseline moderates the efficacy of our intervention.

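### The main secondary outcome is defined in two ways, and the change-from-baseline version rests on a baseline window that ends at the recruiting ED visit, so within-arm falls mislead and precision is lost

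*Protocol article*

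**What the plan says.** The article defines the main secondary outcome twice.

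- Outcomes section: "The main secondary outcome is the change in the proportion of participants with at least one alcohol-related injury (IBC) from baseline to follow-up".
- Abstract, Methods/Design: "the main secondary outcome is the proportion of participants who report any injury related to alcohol in the prior three months".

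The instrument is the Injury Behavior Checklist (IBC). Under Baseline measures: "The IBC asks participants about how often each of the 17 injuries had occurred in the past three months". For each injury affirmed, "subsequent questions about the use of alcohol prior to injury occurrence and whether they were treated by a doctor are asked". No sentence says whether the injury that caused the current ED visit is to be counted or left out.

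Recruitment takes place during an ED visit at three hospitals, "including two Level I trauma centers and one Level II trauma center" (Setting). Injury is not an entry criterion; eligibility under Participants begins with "age 18 to 25 years, English-speaking, hazardous drinking behavior". Follow-up is timed from the visit: "Follow-up data will be obtained through a password-protected website at three-, six- and nine-months after ED discharge".

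The ED physician is asked whether the visit was attributable to alcohol (Baseline measures), and this is planned as a moderator. Statistical analysis plans generalized estimating equations (GEE) with a test of condition and then of intervention by time. It does not say how baseline injury enters the model.

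**The concern.** The baseline and follow-up windows are not sampled alike. The baseline window ends at an ED visit by design; no follow-up window is selected on such a visit. A participant who came in with an alcohol-related injury is positive at baseline because of how the sample was drawn.

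If the outcome is change from that baseline, two things follow. Each arm, control included, can show a fall that is not an effect of anything the trial did, in an outcome meant to show reduced alcohol-related harm. And a comparison of changes carries baseline variation that has little to do with treatment. The two definitions leave open which quantity will be reported.

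**Working it through.** **Plan's own figure.** The article gives no rate, effect size or power for the injury outcome, so there is nothing to reproduce. Its sample size concerns binge drinking days and does not bear on this point.

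**Inputs, all assumed.** p = background three-month risk of an alcohol-related injury, 0.20 (range 0.10 to 0.30). q = share presenting with an alcohol-related injury, 0 to 0.30. ρ = within-person correlation of background injury before the visit and at follow-up, 0.3. The presenting injury is taken as independent of background and later injury, and there is no treatment effect.

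**Step 1: the fall without treatment.** Baseline proportion p0 = 1 − (1−p)(1−q). The follow-up proportion is p, so the fall is p0 − p = q(1−p).

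- q = 0.05: 0.05 × 0.80 = 4 points at p = 0.20 (3.5 to 4.5 over the range of p)
- q = 0.10: 8 points (7 to 9)
- q = 0.30: 24 points (21 to 27)

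This applies equally to all arms in expectation, so the expected difference between arms does not depend on q.

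**Step 2: variance per participant.**

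- Change: p0(1−p0) + p(1−p) − 2(1−q)ρp(1−p)
- Follow-up only: p(1−p) = 0.16
- Follow-up adjusted for pre-visit injury: p(1−p)(1−ρ²) = 0.16 × 0.91 = 0.1456

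Worked case, q = 0.05: p0 = 0.24; change variance = 0.1824 + 0.16 − 2 × 0.95 × 0.3 × 0.16 = 0.2512; 0.2512/0.16 = 1.57 and 0.2512/0.1456 = 1.73.

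| q | p0 | Variance of change | Ratio to follow-up only | Ratio to adjusted follow-up |
|---|---|---|---|---|
| 0 | 0.20 | 0.2240 | 1.40 | 1.54 |
| 0.05 | 0.24 | 0.2512 | 1.57 | 1.73 |
| 0.10 | 0.28 | 0.2752 | 1.72 | 1.89 |
| 0.20 | 0.36 | 0.3136 | 1.96 | 2.15 |
| 0.30 | 0.44 | 0.3392 | 2.12 | 2.33 |

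The row q = 0 is the reference: 1.54 is the general cost of a change score at this correlation. Only the rise above it belongs to the presenting injury.

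**Step 3: adjusting for the IBC as it is collected.** The last column assumes that pre-visit injury can be separated from the presenting injury. If only the IBC as collected is available, the adjusted variance is 0.16(1−r²), with r² = [(1−q)ρp(1−p)]² / [p0(1−p0) × 0.16].

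- q = 0.05: r² = 0.0456²/(0.1824 × 0.16) = 0.071; adjusted variance 0.1486; ratio 0.2512/0.1486 = 1.69
- q = 0.30: r² = 0.0336²/(0.2464 × 0.16) = 0.029; adjusted variance 0.1554; ratio 0.3392/0.1554 = 2.18

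Most of the gain is therefore available from data already collected.

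**Step 4: other values.** At ρ = 0.3 and q = 0.05 to 0.30, the ratio to adjusted follow-up is 0.1627/0.0819 = 1.99 to 0.2853/0.0819 = 3.48 at p = 0.10, and 0.3131/0.1911 = 1.64 to 0.3717/0.1911 = 1.95 at p = 0.30.

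On the trial's scale, 70% of 750 at 2:1:1 leaves about 262 intervention and 131 control completers. With p = 0.20, ρ = 0.4 and an assumed intervention risk ratio of 0.67, the standard error of the difference in change is 0.046 at q = 0, 0.052 at q = 0.10 and 0.059 at q = 0.30. It is 0.041 for follow-up only and 0.037 to 0.040 for follow-up adjusted for the IBC as collected.

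Across p of 0.10 to 0.30, ρ of 0.2 to 0.6 and q of 0.05 or more, the change-score standard error was 0.98 to 1.89 times the unadjusted follow-up one. It was below 1 in one scenario only (p = 0.30, q = 0.05, ρ = 0.6). It exceeded the adjusted one throughout.

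**The case against.** **The affected share is unknown.** A reader might infer that every participant's baseline contains the injury that brought them in, or that the proportion must fall in all arms. The documents do not support that. Injury is not an entry criterion, the Background notes that a quarter of young adults use the ED for primary care, and trauma-center status does not give q. That the presenting injury is counted is itself inferred from the recall window. This objection stands, so the size of the fall cannot be derived from the article.

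**Much of the variance is the ordinary price of change scores.** A reader might attribute the whole of 1.73 to 2.33 to the presenting injury. With q = 0 the ratio is already 1.54. Independence of the presenting injury from later injury is also assumed, which lowers the correlation and raises the ratio. This stands.

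**No change-score test is specified.** Change in a proportion can be read at group level, and GEE with a condition effect need not subtract individual baselines. This stands as to the model. But the outcome is stated as a change, and if baseline is a time point, the intervention-by-time test compares changes. The outcome definition should not depend on that choice.

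**The Abstract may simply be condensed.** The primary outcome is shortened there in the same way. That is plausible, but the two statements still name different quantities.

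**Bias and re-reporting.** A reader might infer a biased arm comparison. Randomization makes the artefact equal across arms in expectation, so none follows. A reader might also infer that the presenting injury is reported again at three months. For an on-time respondent the two windows abut and do not overlap; early or imprecise recall is conjecture.

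**The trial has a control arm and records alcohol-attributable visits.** True, and this limits the harm. The rating is planned only as a moderator, and it concerns the visit rather than an injury.

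**Conclusion.** The point holds in a limited form. The two definitions of the main secondary outcome differ on the page, and this needs no assumption. The change version uses a baseline window that ends at the recruiting visit, with no stated exclusion of the presenting injury. If q is above zero, the presenting injury counts and background risk is stable, each arm falls by q(1−p) without treatment; q is not given.

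The randomized contrast is unbiased. The cost is interpretability of within-arm change and, if change is analysed, precision: at p = 0.20 and ρ = 0.3, a variance ratio to adjusted follow-up of 1.54 at q = 0, rising to 1.73 to 2.33 for q of 0.05 to 0.30. These ratios are illustrative, since p, q and ρ are all assumed. The change is worth making because it costs almost nothing.

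**What to change.** - **Outcomes section:** define the main secondary outcome as the between-arm difference in the proportion with at least one alcohol-related injury at follow-up, consistent with the Abstract.
- **Statistical analysis:** prespecify baseline IBC injury and the physician's rating of an alcohol-attributable visit as covariates in the GEE model for this outcome.
- **Interpretation:** state that within-arm falls from baseline will not be interpreted as harm reduction, and state whether the presenting injury counts at baseline.

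The cost is wording; both covariates are already collected.

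Two additions are optional: a flag for the presenting injury on the baseline IBC, and a three-month item anchored to the date of the ED visit. They would separate pre-visit from presenting injury and guard against re-reporting. But recruitment is under way, so they would change the measure mid-trial, and participants already enrolled would lack the flag.

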### Sample size

For power consideration, we focus on detecting the difference between intervention and control groups in binge drinking days, since it is the primary comparison of interest. Using information from our pilot study [30], if we assume the number of binge drinking days in the intervention group will decrease by a mean of 3.4 (SD 5.4) from baseline to three-month follow-up compared to a decrease of 1.1 (SD 4.1) in the control group, using a sample size ratio of 2:1, we will need 96 participants in the intervention and 48 in the control group to have 80% power to show a difference at significant level = 0.05 based on two-sided two-sample *t* test. Including 48 participants in the assessment group to follow our planned sample ratio 2:1:1, we will need 192 subjects in total. Allowing for a 25% attrition rate, we will actually need to enroll 256 participants in order to achieve a target sample size of 192. If we consider binge drinking days at 9 months, assuming the change will decrease by 35% at 9 months, we need 750 subjects, allowing for 30% attrition. In our pilot, 49% of those screened were hazardous drinkers who scored positive on the AUDIT-C, and 87% of those actually enrolled. So in order to enroll 750 we will thus approach 1760 patients for study participation.

### Statistical analysis

Initially, we will describe the population and all treatment group data graphically and numerically in order to confirm normality for continuous measures, identify expected ranges, detect outliers, and assess data variability. We will specifically examine comparability of treatment groups at baseline, patterns of participant dropout and missing data. In the event that treatment groups differ on baseline sociodemographic characteristics, alcohol-related, and risk-related variables, we will run analyses both with and without these variables as covariates to determine whether baseline differences may account for differences in outcomes. Attrition will be evaluated for systematic differences between patients who complete the research and those who drop out. In this way, we can determine the nature of the potential bias introduced by attrition. Dependent variables will be examined to determine which distributional models are most appropriate. We will use generalized estimating equation analyses for the major study aims and, depending on the nature of the variable, the analyses will use either a normal distribution or negative binomial model for count data (for example, number of binge drinking days). Our models will account for clustering within each subject and each site. If any covariates are identified as necessary during preliminary analyses, these will also be included as covariates. After testing the main effects of condition, we will test interactions between intervention and time to inform us whether differences in alcohol use and consequences outcomes associated with intervention become less or more pronounced over nine months. Following ‘intention-to-treat’ principles, analyses will be conducted on all who were randomized to a condition regardless of whether they actually completed the intervention sessions.

If the intervention does result in significantly lower rates of alcohol use and/or alcohol-related adverse consequences, analyses will be conducted separately to determine whether these effects are mediated by pre-weekend drinking intention and SMS goal-setting patterns. For a variable to be a mediator (a) intervention condition must be significantly related to the intermediate variable; (b) the intermediate variable must be significantly related to alcohol outcome; (c) intervention condition must be significantly related to alcohol outcome; and (d) after controlling for the intermediate variable, the relationship between intervention condition and outcome is significantly reduced. Product of coefficients methods will be used to determine the size and significance of the reduction in the effect of intervention due to inclusion of the mediators. We will also conduct exploratory analyses of potential moderators of the intervention. We will be able to explore whether baseline ED presentation attributable to alcohol and drug use is an important moderator of change in drinking behaviors in addition to the demographic moderators. These will be completed with another set of multivariable regression models. All analyses will be performed with two-sided *P* values considered significant when below 0.05.

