**Discussion:**

This study will test the hypothesis that a mobile phone text-messaging program will result in immediate and durable reductions in binge drinking among at-risk young adults. By testing an intervention group to an assessment-only and control group, we will be able to separate the effect of assessment reactivity. By collecting pre-weekend drinking intentions and post-weekend consumption data in the SA+F group, we will be able to better understand mechanism of change.

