### Randomization

Randomization assignments were generated in blocks of eight for each site by the study statistician and allocated electronically. Randomization sequences are stratified by site in a 2 intervention:1 assessment:1 control ratio to allow for more observations to be available for analyses of mechanisms of change in the intervention group. Participants are blinded to treatment allocation to minimize expectation bias.

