## Discussion

The TRAC study is the first large-scale randomized trial to examine the effectiveness of a text message program for initiating and maintaining reductions in binge drinking among at-risk young adults. If found to be effective, our intervention could be easily scaled-up as a stand-alone program to provide widespread support with minimal disruption to normal clinical practice. Additionally, it could easily be included as a piece in a multi-component intervention, such as a “booster” to traditional in-person counseling interventions. By incorporating longitudinal assessments of drinking behavior in a patient’s natural environment through SMS, stepped-care models could be built where individuals who continue to report hazardous use after program exposure could then be referred directly to a help line or counselor.

There are several potential strengths of our research design worth mentioning. In addition to being large enough to demonstrate reductions in alcohol consumption immediately following intervention (three-month follow-up) as well six months later (nine-month follow-up), we have sufficient power to examine mediators of change associated with this intervention. Inclusion of an assessment-only group minimizes the potential for assessment effects to bias estimates of intervention efficacy. While all participants complete informed consent, where we outline the various treatments they may be subjected to, we do not specifically tell them which one. We believe that this may reduce expectation biases. All baseline measures and outcomes are reported to an automated computer system, potentially increase disclosure of potentially sensitive or embarrassing information, thus reducing reporting biases. By collecting pre-weekend drinking intentions/plans, goal-setting/plan changes, and post-weekend consumption in the intervention group, we will be able to examine “micro processes” or mechanisms of change not previously available in brief intervention studies. Finally, we have made efforts to design our mobile intervention both from a theory-driven approach to behavior change [44] and a user-centered approach [45], which will serve the dual purposes of increasing potential effectiveness as well as reducing intervention attrition.

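### The mediation analysis depends on a significant total effect that an indirect effect does not need, and its two named mediators are collected only in the SA+F arm

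*Protocol article*

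**What the plan says.** All references are to the protocol article.

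- **The aim is unconditional.** The Abstract's Discussion paragraph says of the SA+F intention and consumption data that "we will be able to better understand mechanism of change". The Background says the same, and Outcomes lists the study of mediating processes without any condition. Randomization justifies the 2:1:1 ratio as a way "to allow for more observations to be available for analyses of mechanisms of change in the intervention group".
- **The analysis is conditional.** Statistical analysis opens the mediation paragraph with "If the intervention does result in significantly lower rates of alcohol use and/or alcohol-related adverse consequences, analyses will be conducted separately".
- **Four criteria define a mediator.** Criterion (a) asks for a significant effect of arm on the candidate mediator, and (b) for a significant association between that candidate and drinking. Criterion (c) is that "intervention condition must be significantly related to alcohol outcome". Under (d), adjusting for the candidate has to shrink the arm effect significantly. Product-of-coefficients methods are named for the size and significance of the reduction in (d).
- **Where the mediators are measured.** Statistical analysis names pre-weekend drinking intention and SMS goal setting. The intervention section places both in the Thursday dialog. The SA section says that arm gets no pre-weekend assessment, and the Control section says that arm gets no SMS drinking assessment at all.
- **Power.** The Discussion states that "we have sufficient power to examine mediators of change associated with this intervention". Sample size calculates only the intervention versus control difference in binge drinking days.

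**The concern.** An indirect effect is the product of two paths: arm to mediator (a), and mediator to outcome given arm (b). It can be estimated and tested without a significant total effect. The opening condition and criterion (c) add a test that the question does not need, and an added requirement can only lower the chance of identifying a true mediator. They also confine the analysis to results whose estimated effect passed a significance filter, so the effect being decomposed is on average too large.

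The practical cost falls on a null or borderline result. The useful question then is whether the program failed to shift the intermediate variable, or shifted it without shifting drinking. The between-arm mediation plan would not be run in that case.

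A second fault does not depend on the result. If the named mediators exist in only one arm, criterion (a) has no comparison group.

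**Working it through.** **Inputs (Sample size and Randomization).** Mean decreases 3.4 (SD 5.4) and 1.1 (SD 4.1), so the three-month difference is 3.4 − 1.1 = 2.3 days. Two-sided 0.05. Ratio 2:1:1. At nine months the change is 35% smaller, with 750 enrolled and 30% attrition.

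**1. Reproduce the plan's figure.** Three months, 96 v 48, separate SDs: SE = √(5.4²/96 + 4.1²/48) = 0.809. Then 2.3/0.809 = 2.84, and power = Φ(2.84 − 1.96) = 81% (80.5% by Welch t), against the stated 80%. With attrition, 192/0.75 = 256, as stated.

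Nine months, difference 2.3 × 0.65 = 1.495. For 80% power this needs 635 enrolled with separate SDs, or 760 with a pooled SD of 5.01. The pooled figure is close to the stated 750, so I take 1.495 as the planned effect.

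**2. Power of the total-effect test at N = 750.** This is the ceiling that criterion (c) sets for each outcome. Evaluable at nine months: 750 × 0.70 = 525, of which half is about 262 (SA+F) and a quarter about 131 (control).

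| Case | SE, separate / pooled SD | Difference/SE | Power (noncentral t) |
|---|---|---|---|
| Nine months, 1.495 | 0.490 / 0.536 | 3.05 / 2.79 | 86% / 80% |
| Half that effect, 0.7475 (assumption) | 0.490 / 0.536 | 1.53 / 1.40 | 33% / 29% |
| Three months, 2.3, with 25% attrition (281 v 141) | 0.472 / 0.517 | 4.87 / 4.45 | 99.8% / 99.4% |

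On binge days alone, the test misses in 14% to 20% of trials at nine months and in under 1% at three months, if the planned effects are true.

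**3. Overstatement after the filter.** With z = difference/SE, and the opposite tail negligible, the mean significant estimate divided by the truth is [z + φ(1.96 − z)/Φ(z − 1.96)]/z. At nine months this is 1.08 (z = 3.05) to 1.13 (z = 2.79), an overstatement of 8% to 13%. At half the effect it is 1.71 to 1.85.

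**4. Illustration of the four-criteria rule.** The documents give no path sizes. Assumed: a = 0.3 to 0.5 SD, b = 0.3 to 0.4, linear model, residual SD 1, and the mediator measured in both arms (262 v 131; 6,000 simulations per setting).

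| Total effect | All four criteria met | Product of coefficients alone |
|---|---|---|
| 0.46 SD (three months) | 76% to 99% | 77% to over 99% |
| 0.30 SD (nine months) | 64% to 79% | 77% to over 99% |
| 0.20 SD (smaller than planned) | 40% to 47% | 77% to over 99% |

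**5. Can criterion (a) be tested?**

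| Variable | SA+F | SA | Control |
|---|---|---|---|
| Pre-weekend intention | weekly SMS | not collected | not collected |
| SMS goal setting | weekly SMS | not collected | not collected |
| Behavioral control, drinking norms | baseline and each follow-up | same | same |

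For the two named mediators, (a) has no comparison arm at any sample size. The figures in step 4 are therefore a best case that the plan as written does not reach for them.

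**The case against.** The strongest reply is that this is a conventional causal-steps approach in a secondary analysis and that it costs little here.

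- **The condition is easier to pass than modelled.** It opens on alcohol use and/or consequences, and the main effect comes from GEE over three follow-ups rather than one nine-month t test. If the six-month effect lies midway (an assumption), the average is (2.3 + 1.9 + 1.495)/3 = 1.9 days. With the nine-month SEs, power is then about 94% to 97%. This stands: the 14% to 20% is an upper figure under the planned effects.
- **Three months is a natural mediation endpoint,** since the SMS dialog lasts 12 weeks, and there the loss is small. This also stands.

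Some stronger readings are tempting, but the text does not support them.

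- A reader might infer that the analysis will often be skipped or failed. That needs a smaller true effect or weaker paths than assumed above. The halved effect is not in the document.
- A reader might see two competing rules for mediation. Product of coefficients is the test for (d), not a second rule.
- A reader might conclude that the condition also blocks analyses within SA+F. It governs only whether intervention effects are mediated. The 2:1:1 rationale and the Discussion's remarks on micro processes both refer to the intervention group and can be read as within-arm work without a condition. The ratio is therefore not shown to be wasted.
- A reader might see a conflict between a condition that injuries can satisfy and a criterion on the alcohol outcome. That term is loose enough to include consequences.
- The simulation does not show the power statement to be false, because its path sizes are assumed. It shows only that the statement needs a calculation.

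**Conclusion.** The point holds in a limited form. The significance condition and criterion (c) are unnecessary, sit badly with an aim stated without condition, and can only reduce power. Under the plan's own effects the cost is modest; it becomes large only if the true effect falls well short of plan. The power figures rest on t tests of binge days, 2.3 × 0.65 as the nine-month difference, and the stated SDs and attrition.

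Two further parts need no assumption about effect size. Criterion (a) cannot be tested between arms for either named mediator, and the power statement for mediators has no supporting calculation in the document. The primary comparison is not affected.

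**What to change.** In Statistical analysis:

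1. Delete the opening significance condition, and remove criterion (c) as a requirement.
2. Whatever the primary p value, report path a, path b and the indirect effect, using product of coefficients with a bootstrap confidence interval.
3. Do this for mediators measured in all compared arms. Behavioral control and drinking norms are already collected from everyone at baseline and each follow-up.
4. Describe the intention and goal-setting analysis as within SA+F and exploratory.

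In Discussion, delete the power statement for mediators, or restate it with a calculation and its assumed path sizes.

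The cost is a wording change and some extra analysis, with no change to recruitment or data collection. Mechanism estimates would also be reported after a null result, and must then be labelled exploratory.
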